## Study site

The study will take place in Kisumu, Kenya. Adult HIV prevalence in the Nyanza region where Kisumu is located is the highest in Kenya at 15.1%.As the primary urban and commercial area in Nyanza region, Kisumu has even higher prevalence than many other parts of Nyanza [40]. Identifying new and effective strategies for HIV prevention is therefore urgently needed in this region.

The intervention will be implemented at 3 health centres in Kisumu: the Lumumba Health Centre (LHC), Kisumu East District Hospital (KEDH), and Rabuor Health Centre. LHC is owned and operated by the City Council of Kisumu While both KEDH and Rabuor are government facilities managed by the Ministry of Health (MoH).

LHC facility is one of the largest in the whole of Kisumu County, seeing an average of 400 women per month for ANC and 60 women per month for PPC. Besides the robust ante- and post-natal services, LHC also provides antiretroviral therapy, family planning, HIV counseling and testing, and child immunization. LHC hosted sites for numerous prominent clinical trials, including the University of Illinois-University of Nairobi Kisumu male circumcision trial and the University of Washington-Kenya Medical Research Institute HSV-2 and Partners PrEP trials.

KEDH is a Ministry of health facility in Kisumu within the City of Kisumu, serving mostly residents of the City and its environs. The facility offers both out and in-patient curative services. Other services offeredinclude: Antiretroviral Therapy, Family Planning, HIV Testing and Counseling and, Immunization. About 800 women come to the facility for ANC and 80 women for PPC every month. In the month of October 2014, a total of 998 women received family planning (FP) services from KEDH out of which 382 were seeking FP services for the first time.

Rabuor Health Center is a Ministry of health facility in Kisumu East, sub-county, Kadibo Location. It is about 12 Kilometers from Kisumu town and services offered at the facility include: Antiretroviral Therapy, Family Planning, HIV Counseling and Testing and Immunization, among others. Its catchment area includes, Masogo, Kochieng, Okana, Nyamware South and Nyamware North Locations. Every month the facility serves about 250 and 60 women at the ANC and PPC respectively.

## Study population

We will seek to enroll 600adult women who are attending the health centres’ antenatal or post-partum care clinics. One half of the women in each site will receive the intervention described in this section and the other half will receive the standard of care.

## Inclusioncriteria

To be eligible to receive the intervention, women must meet the following inclusion criteria:

1. 18-39 years of age
2. Primarily resides in or near Kisumu
3. Reports having a current, primary partner (someone that the woman has been in a relationship with for at least 6 months and is identified as her primary partner)
4. Have undergone the opt-out HTC at the ANC or PPC clinic
5. Intends to continue living in or around Kisumu for the next 3 months (follow-up period).

## Exclusion criteria

Participants who meet the following criteria will notbe eligible for enrollment:

1. Male
2. Age <18years or >39years
3. Believes that her partner will hurt her if she gives him an HIV self-test and encourages him to use it
4. Reports having an HIV+ partner
5. Intends to relocate from Kisumu area within the next 3 months

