### Primary Outcome Measures

The primary outcome for the study will be uptake of HIV testing by women’s partnerswithin 3 months of enrollment in the study. For each participant, we will record whether the participant’s partner underwent HIV testing – in the case of the intervention group, this will be a report by female study participants that their partner used a self-test; in the control group, this will be uptake of HTC at the VCT by the partner. We will test for differences in the primary outcome variable between the intervention and control group.

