## Adverse events

Because participants will above all be making voluntary decisions to introduce self-testing with their sexual partners, we do not expect to have significant adverse events related to the usage of the self-test with partners.However, we are concerned about the safety of study participants and have prepared for the unlikely event of violence as a result of introducing the self-test to a sexual partner. During initial enrollment and counseling, we will include referral information regarding services for those experiencing IPVand we will also advise participants to use their best judgment of whether they feel comfortable introducing self-testing with a sexual partner. We are excluding from the study women who express concern that they would experience IPV as a result of suggesting HIV self-test use.Because it is possible that the sexual partners of a participant will react adversely to an HIV-positive test result, we will provide detailed oral and written information to participants on locations where IPV services, confirmatory testing, and HIV care and treatment are available. We will also set up a phone hotline for the study which will be available 24 hours per day. This hotline will be operated by the study staff, who will be available to answer questions related to the study, the use of self-test, as well as locations where participants or their sexual partners can be referred to for IPVservices, for confirmatory testing, and for HIV care and treatment. The telephone hotline will be established for use by the participants free of charge to them. Participants will be asked to “flash” the hotline number, i.e. dial the hotline and disconnect after a single ring thereby alerting the holder of the hotline that the participants is asking to be called back. Alternatively, they will be informed to send “Please call me” and the study coordinator will call them back.

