Every effort will be made to avoid violence. During the training session, participants will be instructed about assessing client behavior and if a participant is concerned that a client will be violent, she will be counseled not to introduce self-testing with that partner. However, violence from partners may occur and there are measures in place to deal with such cases. For example in cases of rape or non-consensual sex, post-exposure prophylaxis can be administered and trauma counseling done at Impact-RDO Drop In Center (DICE) in Kisumu (TumainiNaselica DICE). Participants who experience violence will be referred to Violence Protection Centre at JOOTRH (JaramogiOgingaOdinga Teaching and Referral Hospital, Kisumu) for medical care (if necessary) and psychosocial services. Other options include reporting to the police for possible legal action. All these options will depend on the complainant. All of this information will be shared with participants during the counseling session and also available via the hotline number.

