## Potential risks of proposed research to study participants

We anticipate minimal risks to study participants. Although there is a potential for exposing a participant’s personal information to others during the interview, every consideration will be taken to ensure the interview is conducted in a private place. Study procedures will be thoroughly explained to participants and they will be consented only if they fully understand study procedures and find them acceptable. Participants are allowed to exit from the study at any time.

We do not anticipate any adverse events following the self-testing, outside normal reactions similar to those occurring among persons testing for HIV the first time.These may include negative reactions to an HIV diagnosis or incorrect test results. Participants will be advised to visit a voluntary counseling and testing (VCT)clinic for a confirmatory test as the self-test is a primarily a screening test. The participants will be well trained on self-testing and counseled before being given the test kits. They will also be given a phone number they can call at any time.The information given will instruct the participants about the potential benefits to using the test prior to sex with a partner (for example, knowing partner’s status before sex can lead to better risk reduction). They will also practice and become comfortable using the kits during this session. All of this will take place at the time of enrollment.

There is a risk that sexual partners will react adversely to the participants’suggestions of self-test usage or to the test result itself. To minimize this risk, we will provide detailed information on the need for confirmatory testing and the availability of HIV care and treatment for HIV-infected persons. We will not enroll women who self-report concern that their partner may hurt them if they suggest using the HIV self-test and in addition we will refer men and women who experience violence forto IPV services.

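### The violence-related exclusion is worded at different thresholds in the eligibility list and in the safety text, so a woman who is worried but not certain is eligible under one and barred by the other

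*Protocol*

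**What the plan says.** Three places in the Protocol say who is kept out because of feared partner violence.

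- Exclusion criteria (4.3.2), item 3: a woman is ineligible if she "Believes that her partner will hurt her if she gives him an HIV self-test and encourages him to use it".
- Adverse events (4.7): "We are excluding from the study women who express concern that they would experience IPV as a result of suggesting HIV self-test use".
- Potential risks (5.4): "We will not enroll women who self-report concern that their partner may hurt them if they suggest using the HIV self-test".

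A fourth place concerns women already in the study. Section 4.7, describing the training session, says that "if a participant is concerned that a client will be violent, she will be counseled not to introduce self-testing with that partner".

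Two other parts of the Protocol bear on the consequences. Under Primary Outcome Measures, the event in the intervention arm is "a report by female study participants that their partner used a self-test", while "in the control group, this will be uptake of HTC at the VCT by the partner". Partner violence and other social harms are reported outcomes (Secondary Outcome Measures; Follow-up data; Statistical analysis), and the Justification names the risk of violence as a question the trial should inform.

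**The concern.** Believing that a partner *will* cause harm and being concerned that he *may* are different screening questions and admit different women. Section 5.4 offers its wording as a means of reducing risk, so it reads as a safeguard, yet the formal eligibility list does not deliver it.

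Three things are at stake.

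- **Safety.** Women described as kept out can be let in.
- **Interpretation.** A low rate of partner violence means one thing if worried women were screened out and another if only women expecting violence were.
- **Efficacy, to a lesser degree.** A worried woman in the intervention arm who follows the section 4.7 counselling is unlikely to supply a primary event. No parallel counselling is described for the control arm.

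**Working it through.** **Comparing the wordings**

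| Place | State of mind | Certainty of harm |
| --- | --- | --- |
| Exclusion criteria, item 3 | belief | will |
| Adverse events (4.7) | concern | would |
| Potential risks (5.4) | concern | may |

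Take a woman who is concerned that her partner may hurt her but does not believe that he will. Item 3 leaves her eligible. Section 5.4 bars her. Section 4.7 arguably bars her too, because it turns on concern, although its *would* is closer to item 3 than to section 5.4. The clear conflict is between item 3 and section 5.4. Research assistants screen for eligibility (Sampling), but the screening questionnaire appears only as a title (Appendix 1), so the question actually asked cannot settle the matter.

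**Does the conflict touch the primary comparison?**

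Screening, consent and the baseline interview come before randomization (Baseline data collection; Randomization). Both arms therefore draw on the same screened women, and allocation is unaffected. What remains is possible dilution in the intervention arm.

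Inputs: 20% control uptake against 30%, with 300 women per group (Sample size justification). A two-sided 5% level is assumed for the power calculation, because the Protocol states that level only for its other comparisons. The formula is the normal approximation for two proportions, with no continuity correction and no design effect:

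power = Φ{ [ |p2 − p1| − 1.96 √(2 p̄(1 − p̄)/n) ] / √( [p1(1 − p1) + p2(1 − p2)]/n ) }, where p̄ = (p1 + p2)/2.

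The Protocol's own figure, with p1 = 0.20, p2 = 0.30 and n = 300:

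- The standard error under no difference is √(2 × 0.25 × 0.75/300) = 0.0354.
- The standard error under the alternative is √((0.16 + 0.21)/300) = 0.0351.
- Power = Φ{(0.10 − 1.96 × 0.0354)/0.0351} = Φ(0.874) = 80.9%. The stated 80% is reproduced.

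Now let f be the share of enrolled women who are worried but not certain. The Protocol gives no value, so 2%, 5% and 10% are **assumptions**. All such women in the intervention arm are assumed to follow the counselling. Three cases:

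- **A.** They supply no events in the intervention arm: p2 = 0.30(1 − f), control held at 0.20.
- **B.** Their partners in the intervention arm test at the control rate: p2 = 0.30(1 − f) + 0.20f, control held at 0.20.
- **C.** They supply no events in either arm: p1 = 0.20(1 − f), p2 = 0.30(1 − f).

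| f (assumed) | A: rates, power | B: rates, power | C: rates, power |
| --- | --- | --- | --- |
| 2% | 20% v 29.4%, 76% | 20% v 29.8%, 79% | 19.6% v 29.4%, 80% |
| 5% | 20% v 28.5%, 68% | 20% v 29.5%, 77% | 19.0% v 28.5%, 78% |
| 10% | 20% v 27.0%, 53% | 20% v 29.0%, 73% | 18.0% v 27.0%, 75% |

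The result depends more on how these women behave in each arm than on the discrepancy itself, and the Protocol supplies neither their share nor their behaviour. The table shows the direction and spread of a possible effect. It is not an estimate.

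**The case against.** The strongest reply is that sections 4.7 and 5.4 are narrative text that loosely restates item 3, and that the screening questionnaire may already ask one clear question. That cannot be ruled out. It means that worried women *can* be enrolled, not that they *are*. It does not remove the conflict: the eligibility list is the formal rule, section 5.4 states a different one, and nothing visible says which governs.

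A reader might also infer that the counselling sentence in section 4.7 proves that worried women are enrolled, since under section 5.4 there should be none. The Protocol does not support that. The sentence is set in the training session, where concern may first arise after screening. A screen followed by a counselling backstop is layered protection, consistent with the statement under Intervention group that women need not suggest the test. The word *client* does not fit antenatal and postpartum women, so the sentence is weak evidence about who is in this trial.

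A reader might further take 53% as the likely power. That is the extreme of the range. It needs an assumed 10% share, no intervention-arm events among these women, and a control rate left at 20% although the same women are equally present there. Moreover, 30% is the smallest increase the trial was sized to detect, in an intervention that always left women free not to offer the kit. Subtracting non-users from it may count non-use twice. This part of the objection stands, so the power figures do not carry the point.

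**Conclusion.** The Protocol contradicts itself on who is excluded for feared partner violence. The clearest conflict is between item 3 of the Exclusion criteria and section 5.4; section 4.7 adds a third wording. If item 3 is applied literally, women whom the safety text says are kept out can be enrolled, and the population behind the violence and social-harm results is not defined. This conclusion rests on the wording alone.

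The number of women affected cannot be determined from the Protocol. Any effect on the primary comparison is dilution towards no difference, of unknown and possibly small size. Over assumed shares of 2% to 10%, power runs from 76% down to 53% in the least favourable case and from 80% down to 75% in the mildest, against 80.9% with none. There is no bias in allocation. The conflict should be resolved because it concerns a stated participant protection and costs almost nothing to correct, not because a loss of power has been shown.

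**What to change.** Reconcile item 3 of the Exclusion criteria, the exclusion sentences in sections 4.7 and 5.4, and the screening questionnaire (Appendix 1) to one exclusion rule in the same words. The sponsor and the ethics committees should choose the threshold; the Protocol does not settle it and this review does not propose one. State whether the counselling in section 4.7 applies only to concern that arises after enrolment, and replace the word *client* with a term that fits this population. Report the violence and social-harm results with the chosen rule stated beside them.

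The cost is one reworded criterion, one screening item and matching edits to the safety text. Depending on the threshold chosen, a few more women may be screened out before 600 are enrolled.

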## Sampling

Research Assistants (RAs) will invite eligible individuals to participate in the study.Recruitment of participants will take place at the Lumumba Health Centre in Kisumu, Kisumu East District Hospital and Rabuor Health center. Staff at the ANC and PPC clinics will inform patients as they are being discharged home that there is a study they may qualify for; if they express interest in learning more, they will be given a referral coupon to take to the study staff based at the facility. For ANC and PPC patients, the referral coupons will be identical and will have a unique number rather than the women’s names or any other identifying information. Before issuing the coupon to women, the ANC and PPC staff will write down a discreet code for whether the woman is HIV-positive or HIV-negative (OP for HIV-positive and ON for HIV-negative). Only the study and clinic staff will know what the codes denote. We believe the coding system will be discreet enough to not disclose the HIV status to unauthorized person(s). This information will be necessary for assessing participation rates in the study by HIV-positive and HIV-negative women, analyzing use of self-testing by HIV status, and for sampling HIV-positive and HIV-negative participants in qualitative interviews. Once the RAs collect the referral coupons from the women, the number on the coupon and the HIV status code on the coupon will be recorded on secure tablets. No identifying information will be collected for women who decline to participate in the study.

Women at all stages of pregnancy and post-partum care will be referred to study RAs. The study RAs will then explain the study to women, screen them for eligibility for the study, and ask those who are eligible if they are willing to participate in the study. RAs will obtain informed consent and enroll the woman into the study. We will conduct recruitment in the study facilities in a manner that ensures the number of participants in each facility is proportional to the number of women who seek care at each facility.

During the qualitative phase of the study, we will purposively sample a sub-set of about 45 study participants. We will seek to include 10-15 women who tested together with their partners (couples testing), 10-15 women who gave the test to their partner to use (partner testing), and 10-15 women who never used the test or gave it to their partner to use.We will sample from among all study sites and both ANC and PPC clients.

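### The HIV status code on the referral coupon is a fixed two-value mnemonic, so the assurance that only staff can read it is not secured

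*Protocol*

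**What the plan says.** The procedure is set out in the Protocol, section 4.4 Sampling. Clinic staff mention the study to women at discharge, and those who want to hear more receive a coupon: "they will be given a referral coupon to take to the study staff based at the facility". For antenatal and postpartum patients alike, "the referral coupons will be identical and will have a unique number" in place of a name or other identifier. Before handing it over, staff "will write down a discreet code for whether the woman is HIV-positive or HIV-negative (OP for HIV-positive and ON for HIV-negative".

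That the code is on the coupon itself is clear from the next step. After research assistants have taken the coupons in, "the number on the coupon and the HIV status code on the coupon will be recorded on secure tablets".

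Two statements address confidentiality. One is a flat assertion: "Only the study and clinic staff will know what the codes denote". The other is a judgement: "We believe the coding system will be discreet enough to not disclose the HIV status to unauthorized person(s".

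The section gives three uses for the status information: participation rates by HIV status, analysis of self-test use by status, and sampling for the qualitative interviews.

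**The concern.** A code protects a carried document only if someone who sees it cannot tell what it means. Here the code takes two values, and the letter that varies stands for positive or negative. The people carrying it have, for the most part, just learned the fact it encodes. If the meaning can be worked out, the coupon shows a woman's HIV status on paper at a point where she has not yet been screened for the study or consented to it.

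What is at stake is privacy and participant safety in a setting where the Protocol's own background section lists stigma and fear of disclosure among the barriers to testing. No estimate or test in the trial depends on it.

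**Working it through.** No arithmetic applies. The check sets the relevant parts of the Protocol side by side.

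1. **How much the code conceals.** Sampling gives two codes, OP and ON. The first letter is constant. The second is P for positive or N for negative. No variation by woman, day or site is described, so learning what one code means gives the meaning of the other.

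2. **Who can decode it.** Inclusion criterion 4 requires that a woman has undergone opt-out HIV testing at the clinic, and staff can write a code only if her status is known to them. A woman who has been told her result can match it to the letters on her coupon. So the statement that "Only the study and clinic staff will know what the codes denote" does not follow from the procedure. A third party who sees a single coupon has no key, but could readily guess.

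3. **Where the coupon goes.** It is issued by the clinic, carried by the woman to study staff at the same facility, and collected there by the research assistants, who then explain the study, screen and seek consent. For a woman who presents, the exposed interval is the time between the clinic and the study staff.

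4. **What happens if she does not present.** Nothing is said about coupons that are not handed in. A woman who accepts one and then leaves keeps a paper with her code on it.

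5. **Whether another section closes the gap.** Section 5.3, Protecting privacy and confidentiality, covers staff training, confidentiality agreements, participant codes, encrypted devices and locked storage. It does not mention the referral coupon.

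6. **Whether the code must be on the coupon.** Each coupon already has a unique number. A list linking number to status gives the research assistant the same information, so all three stated uses can be met without it.

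7. **A side effect on the participation rates.** Number and code are recorded only once a coupon is collected. The status of women who take a coupon and never present is not described as captured, although participation by status is one of the stated purposes. A list made when the coupon is issued would capture it.

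**The case against.** The strongest reply is that the exposure is small and the Protocol has already reduced it. The coupon has no name, goes only to women who ask to learn more, stays within one facility in the ordinary course, and is taken back by the research assistants. A woman decoding her own coupon learns nothing new. The Protocol also presents discretion as a belief, does not claim that the risk is eliminated, and sets the procedure out openly for two ethics bodies. All of this stands, and it narrows the point. It does not rescue the assertion that only staff will know the codes, and it does not cover coupons that are never returned.

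A reader might infer several stronger things that the document does not support:

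- **That anyone holding a coupon can read it.** A stranger with one nameless slip may guess the meaning but cannot be certain, and the document does not show what else is printed on it.
- **That about 90 women are exposed.** Applying the 15.1% regional adult prevalence under Study site to 600 women gives 600 × 0.151 = 90.6. But those 600 are enrolled women, whose coupons are collected on site, and regional prevalence need not hold for them. The group that could take a coupon away is women who do not present, and its size is not given.
- **That women excluded because they fear their partner leave with a coded slip.** The research assistants who collect the coupons also do the screening, so such a woman has already reached the collection point.
- **That the Protocol's risk section concedes this disclosure.** Section 5.4 does say that "there is a potential for exposing a participant’s personal information to others", but that sentence is about privacy during the interview.

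The vouchers and referral coupons later given to the two study groups are separate documents and are not said to carry the status code.

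A list of number and status is itself sensitive, and it would include women who never approach the study. That is a fair cost to weigh against the change.

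**Conclusion.** The point holds as a limited privacy weakness. A fixed, two-value mnemonic code on a coupon that the woman carries does not secure the confidentiality that Sampling asserts. The remaining exposure is mainly while the coupon is carried within the facility, and for women who take one and do not present. Their number is not in the document, so no count of women exposed can be stated.

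The conclusion assumes that women coded by the clinic have been told their result, which is the normal consequence of the testing required for eligibility. It also assumes that the coupon is an open slip, since no sealing or masking is described. There is no effect on sample size, power, error rate or the primary analysis. The change is worth making because it is cheap and keeps every stated use of the data.

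**What to change.** In section 4.4, remove the status code from the referral coupon. Have clinic staff record the coupon number and HIV status, without names, on a secured list or encrypted tablet kept at the facility. After collecting a coupon, the research assistant looks up the status by number and records it as now planned. Delete the two sentences on the discretion of the codes, and add the list to the safeguards in section 5.3.

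Participation by status, analysis by status and qualitative sampling are all preserved. The status of coupon recipients who never present is captured as well, which improves the denominator for participation rates. Because the list holds no names, the commitment not to collect identifying information on women who decline is kept.

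The cost is some look-up work for staff and one more nameless list to secure at each of the three facilities.
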